## Abstract

**Background:**

Many low- and-middle-income countries are disproportionately burdened by cervical cancer, resulting in high morbidity and mortality. HPV-DNA testing coupled with treatment with thermal ablation is a recommended screening and precancer treatment strategy, but not enough is known about how this can be effectively implemented in the context of integrated services. The (Scale Up Cervical Cancer Elimination by Secondary prevention Strategy, (SUCCESS) project is conducting a study to understand this approach, integrated into existing women’s health services in Burkina Faso, Cote d’Ivoire, Guatemala, and the Philippines (2020–2024).

**Methods:**

A hybrid effectiveness-implementation type III mixed-methods observational study design is used to assess feasibility, acceptability, and costs of integrated service delivery in 10 sites per country, selected considering urban/rural location, facility level, onsite/offsite laboratories, and health services type. In each country, a sample size of 2227 women aged 25–49 years will be enrolled with about 20% being women living with HIV. The primary outcome is proportion of HPV positive women completing precancer treatment, if eligible, within three months of screening. Data collection and analysis includes; facility and client exit surveys, key informant and client interviews, registries and project records extractions, and costing data analysis. Analysis includes descriptive statistics, context description, thematic analysis, and document analysis. Quantitative analyses will be stratified by participant’s HIV status.

**Discussion:**

Recruitment of study participants started in April 2022 (Burkina Faso and Côte d’Ivoire) and August 2022 (Guatemala and the Philippines). Enrolment targets for women screened, client exit, in-depth and key informant interviews conducted were reached in Burkina Faso and Cote d’Ivoire in November 2022. Guatemala and Philippines are expected to complete enrolment by June 2023. Follow-up of study Participants 12-months post-treatment is ongoing and is expected to be completed for all countries by August 2024. In LMICs, integrating cervical cancer secondary prevention services into other health services will likely require specific rather than incidental recruitment of women for screening. Reconfiguration of laboratory infrastructure and planning for sample management must be made well in advance to meet induced demand for screening.

*Trail Registration* ClinicalTrials.Gov ID: NCT05133661 (24/11/2021).

**Supplementary Information:**

The online version contains supplementary material available at 10.1186/s12978-023-01696-8.

## Background

Cervical cancer is the fourth most common cancer among women globally. It is the leading cause of death among women living with HIV infection [1–3]. 90% of cervical cancer-related deaths occur in low- and middle-income countries (LMICs), where there is often under-resourced healthcare infrastructure [4]. Based on available evidence over the past decade showing that HPV testing is more sensitive and reliable for the detection of cervical intraepithelial neoplasia compared to cytology and visual inspection with acetic acid (VIA), the WHO recommends using high-performance molecular testing for primary screening [1]. Continued use of VIA for primary screening is therefore not considered to be an effective strategy for scaling up cervical cancer prevention and treatment services especially in LMICs [5–7]. Offering timely cervical cancer secondary prevention measures with new technologies such as HPV test for primary testing and thermal ablation for pre-cancerous lesions treatment, through integration into existing primary health programs may improve access, and provide a platform for population-based screening. Some LMICs like the Philippines [8], having developed national cervical cancer screening programs and others, like Tanzania and Nigeria have costed strategic plans to guide implementation [9]. In resource-limited settings, critically needed services like HPV DNA testing might be expanded through a strategy of integrating them into existing services that are well-established, trusted and related in terms of operations, for example family planning [10, 11]. However, there is limited evidence globally on effective implementation strategies for providing cervical cancer prevention and treatment services at scale as part of integrated health services.

The SUCCESS (Scale Up Cervical Cancer Elimination by Secondary prevention Strategy) project is a Unitaid-funded a consortium led by Expertise France in collaboration with Jhpiego and UICC. The implementation research component of the project is designed to facilitate the generation of evidence regarding the introduction of HPV-DNA testing and pre-cancer treatment through thermal ablation in Burkina Faso, Cote d’Ivoire, Guatemala and the Philippines [12].

The goal of the study is to generate evidence on the feasibility, acceptability, and cost of integrating the HPV plus thermal ablation strategy into the four existing health systems. The study is embedded in the project activities and aims to answer crucial implementation questions identified by the WHO as highly relevant to low-resource settings. SUCCESS thus aligns strategically with the WHO call for the global elimination of cervical cancer in generating information that will contribute towards reaching the 2030 cervical cancer elimination goals.

This paper describes the approach and process employed by SUCCESS project to understand the acceptability and feasibility of providing HPV DNA testing and treatment of pre-cancer cervical lesions with ablative treatment for women 30–49 years in the general population and among women living with HIV (WLHIV) aged 25–49 years as recommended by WHO [13]. The findings of the study will inform the country strategy and guidelines on offering integrated quality cervical cancer secondary prevention services in a manner that is culturally sensitive, client oriented, and system appropriate.

## Methods/design

### Design

This is a hybrid effectiveness implementation Type III study [14], using mixed methods approach for data collection. It’s multi-country, conducted across three continents (Africa, Asia, and Central America), and registered in the ClinicalTrials.gov registry—ID# NCT05133661 (24/11/2021). The implementation research conceptual framework was modelled on the approach described by Proctor et. al, is shown in Fig. 1 [15]. Specifically, we closely observe and study locally relevant contexts and processes, to understand the implementation of services and client outcomes.

**Fig. 1 Fig1:**
[figure not shown]
Implementation research conceptual framework for SUCCESS HPV study

The primary outcome is the proportion of HPV positive women (general population and WLHIV) who undergo treatment for precancerous cervical lesions within three months of screening—the optimal time for quality services. Acceptability of services is assessed through measuring satisfaction positive perceptions, and uptake of the cervical cancer services by the users and the service providers. Feasibility of implementation measures the practicability of providing the cervical cancer services through the mechanisms that exist in the four study countries. The unit cost of providing the services as well as user out-of-pocket cost will be also be determined.

### Research questions

The overall research question is: When integrating HPV screening and treatment of pre-cancer lesions with ablative treatments into reproductive health and HIV services, what factors affect the feasibility and acceptability among screen-eligible women and facility-level health care providers in each of the four countries?

Specific research questions are:How feasible is it to implement integrated HPV testing (including self-collection of samples) and ablative treatment of pre-cancerous cervical lesions among HPV positive women aged 30–49 years (general population) and 25–49 years (WLHIV), leveraging on the existing health systems in the four study countries?What is the acceptability of HPV screening through self-collection or clinician collection of sample, and ablative treatment of precancerous lesions among women accessing cervical cancer services, and among service providers in the study sites?What is the cost of implementing integrated HPV screening and cervical precancer treatment services (Supply: counselling, HPV testing, treatment, training health care providers, etc.), and user-related costs (travel, out of pocket expenses opportunity costs, etc.) in the SUCCESS project supported sites?Which factors influence the successful implementation of integrated HPV screening and treatment services (e.g. perceptions, experience of care, religious beliefs, culture, individual characteristics, availability of services, cost, etc.) in the four study countries?

### Setting

In each country, 10 study sites were selected considering a balance of location (e.g. rural/urban), level of services (primary/secondary/tertiary), workload at various service delivery points in a facility (e.g. HIV, postnatal, maternal and new-born health clinic), and the laboratory services available (onsite/ offsite). Where multiple facilities met the criteria, proportionate allocation of the sample was done to achieve balance.

### Participants and sampling

The study relies on multiple approaches to answer the research questions which in turn necessitates the use of different approaches to sampling of the relevant study sub-populations. The four sample components are presented.

Prospective component: In each country, we are enrolling at the time of screening 2,227 women (general population [1787] and WLHIV [440]) and following for 12-months post-treatment those among them who test HPV positive. Assuming an average HPV positivity rate of 15%, we computed that we will follow 268 and 141 from general population and WLHIV, respectively. This will help us to determine the proportion who complete screen-to-treat cycle within three months of screening—the primary outcome of the study. The sample size was computed to a precision of ± 5% and power of 80 percent, design effect of 2 due to clustering at health facilities, and adjusted for loss to follow up at 20%.

Cross-sectional component: To assess the client experience of care and collect some cost data from the user’s perspective, a sample size of 125 women per country was computed assuming that about 1,000 women are available to participate in client exit interview after HPV screening and enrolment, during a 3-month enrolment period (https://www.radar-project.org/isaqoc) [16].

Qualitative data: Fifty in-depth interviews (IDIs) among women who either accept or decline screening/treatment are being conducted in each country. In addition, sixty-eight key informant interviews (KIIs) among service providers, health facility and program managers, policy makers, community mobilizers and men in the community are being conducted. The qualitative data will be triangulated with the quantitative data to help us understand contextual factors that affect implementation of HPV DNA testing and treatment at scale.

Cost data: In addition to the client exit interview cost data, additional data are being collected through time-and-motion observation to document inputs at service delivery (e.g. staff time, supplies, number of procedures per day, laboratory-related processes etc.). Project financial records for 2022–23 will be analysed. The cost database will be maintained using a modified version of the C4P costing tool [17].

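### The stated 15% HPV positivity gives 66 women living with HIV to follow per country, not 141: either the stated assumption is wrong (likelier) or the planned count is about twice too high

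*Protocol article*

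**What the plan says.** The prospective component, under Participants and sampling in the protocol article, sets the enrolment per country: "In each country, we are enrolling at the time of screening 2,227 women (general population [1787] and WLHIV [440". The abstract agrees on the split: "a sample size of 2227 women aged 25–49 years will be enrolled with about 20% being women living with HIV". Follow-up is limited to a subset of those enrolled, described as "following for 12-months post-treatment those among them who test HPV positive". The size of that subset is then given: "Assuming an average HPV positivity rate of 15%, we computed that we will follow 268 and 141 from general population and WLHIV, respectively".

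The same paragraph ties these women to the primary outcome, the share completing screening and treatment within three months. It cites a precision of ±5%, 80% power, a design effect of 2 for clustering by facility and a 20% allowance for loss to follow-up. The abstract adds that quantitative analyses are stratified by HIV status. The article gives no other positivity rate, for WLHIV or for anyone else.

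**The concern.** The article states one positivity rate, applies it to two enrolment figures and reports two results as computed from it. Only one of the two results follows. The WLHIV figure is more than double what the stated rate gives.

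The figure matters because HPV-positive women form the denominator of the primary outcome and the analysis is stratified by HIV status. The 141 is therefore the planned size of the WLHIV stratum in each country. As the sentence stands, a reader cannot tell whether to expect about 66 or about 141 women there, and so cannot judge how precise the WLHIV estimate will be.

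**Working it through.** **Inputs**, all from Participants and sampling unless noted: 1787 general-population women and 440 WLHIV enrolled per country (total 2227); positivity 15%; women to follow 268 and 141 (sum 409); design effect 2; loss 20%. Ten sites per country comes from Setting.

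**Step 1. Reproduce the stated counts** as enrolled × positivity.
- General population: 1787 × 0.15 = 268.05. The stated 268 is reproduced.
- WLHIV: 440 × 0.15 = 66.0. The stated 141 is not reproduced; 141/66 = 2.14.

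**Step 2. Read 15% as a pooled average.**
- 2227 × 0.15 = 334, against the stated sum of 409.
- 409/2227 = 18.4%.
- With the general-population count fixed at 268, a pooled 15% leaves 334 − 268 = 66 WLHIV, as in step 1.

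**Step 3. Try the adjustments named in the same paragraph on the 66.**
- Loss: 66/0.8 = 82.5, or 66 × 1.2 = 79.2.
- Design effect: 66 × 2 = 132.
- Both: 66 × 2/0.8 = 165, or 66 × 2 × 1.2 = 158.4.

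None gives 141. Any such adjustment would also have to apply to WLHIV alone, because 268 is the unadjusted 15%.

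**Step 4. Solve back from 141.**
- Implied positivity: 141/440 = 32.0%, and 440 × 0.32 = 140.8, which rounds to 141.
- Implied enrolment at 15%: 141/0.15 = 940 WLHIV, against 440.

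**Step 5. Effect on precision, for illustration.** The 95% half-width is 1.96 × √(p(1 − p) × 2/(0.8 n)), where n is the number of HPV-positive WLHIV. The completion proportion p is an assumption, because the article gives none. Taking the 20% loss off the followed women is also my reading.

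| HPV-positive WLHIV | After 20% loss | p = 0.8 | p = 0.5 |
|---|---|---|---|
| 66 | 52.8 | ±15.3 points | ±19.1 points |
| 141 | 112.8 | ±10.4 points | ±13.0 points |

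For example, with 66 women and p = 0.8: 1.96 × √(0.16 × 2/52.8) = 0.153.

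**Step 6. Sensitivity to the design effect.** If the design effect is 2 at 141 women over 10 sites (14.1 per site), the intracluster correlation is 1/(14.1 − 1) = 0.076. At 6.6 women per site the design effect is then 1 + 5.6 × 0.076 = 1.43. The half-width at p = 0.8 becomes 1.96 × √(0.16 × 1.43/52.8) = 0.129, about ±13 points.

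**The case against.** The strongest reply is that no shortfall exists. Both stated counts are clean products of a round rate and the stated enrolment: 15% of 1787 and 32% of 440. The natural explanation is that two stratum rates were used and the article merged them into one figure mislabelled as an average. The full protocol, which the article condenses, may well give both. In that case 440 and 141 both stand, and no enrolment target or analysis changes. I think this explanation is the likelier one. It remains an inference, and it does not excuse the sentence, which names one rate and says that both counts were computed from it.

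A reader might go further and infer that the WLHIV stratum cannot support a useful estimate in any one country. The article does not support that. It sets no minimum precision for the stratum and does not say that ±5% applies within strata. On the illustrative figures, 141 women also fall well short of ±5%, so the discrepancy widens a gap that is there under either count; it does not create it.

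The half-widths are also open to challenge. They rest on assumed completion proportions and on holding the design effect at 2 for both counts. With fewer women per site the design effect would probably be smaller, which brings ±15 nearer to ±13 at 80% completion. They show scale only.

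Finally, enrolment targets had been reached in two countries, and one might want the observed HPV-positive counts beside the planned ones. Correcting a planning sentence does not require them.

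**Conclusion.** The sentence is wrong as written. At the stated 15%, 440 WLHIV yield 66 HPV-positive women per country, not 141, a factor of 2.14. The pooled rate implied by the stated counts is 18.4%, not 15%. No weighting, loss or design-effect adjustment that I tried reconciles them. This part uses only the article's own figures.

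The article does not show which figure is at fault. The likelier error is the stated assumption: 15% would be the general-population rate, and a WLHIV rate of about 32% was left out. The alternative is that 15% was meant for both groups, in which case the planned WLHIV denominator of the primary outcome is about twice too high. A reader might take the mismatch as proof that too few WLHIV are being enrolled; it is not. Only under the alternative does the WLHIV half-width widen, from about ±10 to ±15 points at 80% completion or from ±13 to ±19 at 50%, given a design effect of 2, 20% loss and those assumed proportions.

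**What to change.** Check which rates were used in the sample-size calculation, then correct the one sentence.

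- If stratum rates were used, state them: 15% for the general population, about 32% for WLHIV and about 18% pooled. The counts of 268 and 141 stay, and 15% is no longer called an average.
- If 15% was meant for both groups, restate the WLHIV count as 66 and the total as 334. Give the precision expected for the WLHIV stratum, with the completion proportion and design effect assumed.

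The first case costs a rewording and changes nothing in the design. The second costs a corrected count and a short precision statement.

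### The stated ±5% precision is not met in either HIV stratum of a country unless completion is very high: with design effect 2 and 20% loss, about 92.5% (268 women) and 96.2% (141 women)

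*Protocol article*

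**What the plan says.** The Protocol article, Participants and sampling (prospective component), enrols 2,227 women in each country: 1,787 from the general population and 440 WLHIV. It continues: "Assuming an average HPV positivity rate of 15"%, "we computed that we will follow 268 and 141 from general population and WLHIV, respectively". These women supply the primary outcome, the proportion treated within three months of screening.

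The basis for the size is given in one sentence: "The sample size was computed to a precision of ± 5% and power of 80 percent, design effect of 2". The same sentence attributes the design effect to clustering at health facilities and says that the size was "adjusted for loss to follow up at 20"%. It gives no expected completion proportion, no confidence level, and no null value or difference to which the power could refer.

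The Abstract (Methods) adds: "Quantitative analyses will be stratified by participant’s HIV status".

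**The concern.** The inputs and the result stand in the same paragraph and do not appear to fit. A half-width of 5 points under a design effect of 2 and 20% loss normally needs several hundred women per stratum, and 141 is well short of that unless the proportion is close to 100%.

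This sentence is the article's only justification for the size of the primary analysis. Results are to be stratified by HIV status and are meant to inform Ministries of Health. A reader who takes it at face value would expect each country's completion rate to be known to within 5 points. At 80% completion the intervals would be about 1.5 times (general population) and 2.1 times (WLHIV) that wide.

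**Working it through.** **Inputs from Participants and sampling:** 268 and 141 HPV-positive women per country; 409 together; precision ±5 points; design effect 2; loss 20%; HPV positivity 15%; enrolment 1,787 and 440.

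**Assumptions, because the article does not state them:** 95% two-sided confidence; completion proportion p shown over a range.

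**Step 1. Where 268 and 141 come from.**
- 1,787 × 0.15 = 268.05, and 268 / 0.15 = 1,786.7, which rounds up to 1,787. So 268 is the gross count of positive women, and no extra inflation for design effect or loss sits between it and enrolment.
- 440 × 0.15 = 66, not 141. The figure 141 implies 141 / 440 = 32% positivity in WLHIV, which is not stated.

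**Step 2. Trying to reproduce the counts.**
- Precision formula: n = 1.96² p(1−p) / 0.05² × 2 / 0.8. This gives about 960 at p = 0.50, 615 at 0.80, 346 at 0.90 and 183 at 0.95. No p on a 5-point grid gives 268 or 141 once both the design effect and the loss are applied.
- A form that combines precision and power does match: n = (1.645 + 0.842)² p(1−p) / 0.05² × 1.2. At p = 0.90 it gives 222.57 × 1.2 = 267.1, hence 268. At p = 0.95 it gives 117.47 × 1.2 = 140.96, hence 141. Both matches need design effect 1. With design effect 2 the formula gives 534.2 and 281.9, hence 535 and 282.

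**Step 3. Precision that the counts deliver.** Effective size = n × 0.8 / 2, so 268 gives 107.2, 141 gives 56.4 and 409 gives 163.6. Half-width = 1.96 √[p(1−p) / effective size], in percentage points:

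| p | General population (268) | WLHIV (141) | Both strata, one country (409) |
|---|---|---|---|
| 0.50 | ±9.5 | ±13.0 | ±7.7 |
| 0.80 | ±7.6 | ±10.4 | ±6.1 |
| 0.90 | ±5.7 | ±7.8 | ±4.6 |
| 0.95 | ±4.1 | ±5.7 | ±3.3 |

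**Step 4. Completion needed for ±5.** Set p(1−p) = 0.05² × effective size / 1.96².
- 268: p(1−p) = 0.0698, so p ≥ 0.925.
- 141: p(1−p) = 0.0367, so p ≥ 0.962.
- The mirror values near zero also satisfy the equation, but they are not a sensible planning range for treatment completion.

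**Step 5. Sensitivity.**
- Women lost counted as untreated, so that only the design effect applies (effective sizes 134 and 70.5): ±5 needs p ≥ 0.903 and p ≥ 0.952. The half-widths at 0.80 are ±6.8 and ±9.3.
- 90% confidence, with design effect and loss: ±5 needs p ≥ 0.889 and p ≥ 0.945.
- 66 WLHIV instead of 141 (effective size 66 × 0.8 / 2 = 26.4): ±19.1 at p = 0.50, ±15.3 at 0.80 and ±11.4 at 0.90.

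**The case against.** The best defence is that the article is a condensed report. The expected proportions may stand in the full protocol, and they may be high and differ by stratum. That carries weight. With p = 0.925 and p = 0.962, both strata meet ±5 under the stated design effect and loss. So a reader who infers that one common ±5% cannot hold for two strata of such different size would be wrong. The match in Step 2 itself points to planning values of 0.90 and 0.95, which makes the half-widths at 50% to 80% less central than they look. But the stated precision still fails at those values: ±5.7 for 268 at 0.90, and ±5.7 for 141 at 0.95.

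Second, the primary outcome closes three months after screening while follow-up runs to 12 months after treatment, so loss need not shrink the denominator. If women without recorded treatment count as not completing, the half-width is ±5.1 for 268 at 0.90 and ±5.1 for 141 at 0.95, close to the claim. This helps only if most of the loss comes after the three-month point. If 20% were lost before it and counted as untreated, completion could not exceed 1 − 0.20 = 80%, where the half-widths are ±6.8 and ±9.3.

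Third, the sentence does not say that ±5% applies per stratum. Taken for the country total of 409, it holds from about p = 0.88. That stands as a possible reading, but the separate counts and the stratified analysis make the stratum reading the natural one, and at 80% the total still gives ±6.1.

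On power, a reader might test a 5-point difference from a fixed value and report 11% to 37% power. The article states no such hypothesis, so a power shortfall cannot be shown. The fault is that the 80% refers to nothing.

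**Conclusion.** The point holds as a conditional statement. At 95% confidence, with the article's own design effect and loss, 268 and 141 women per country do not give ±5 points per HIV stratum unless completion is at least about 92.5% and 96.2%. If women lost are counted as untreated, the limits are about 90.3% and 95.2%. Below them the shortfall is material: ±7.6 and ±10.4 at 80% completion, ±9.5 and ±13.0 at 50%.

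Two related faults in the same paragraph are certain without any assumption: the 80% power has no stated hypothesis, and 141 WLHIV contradicts 15% of 440 = 66. If 66 is right, WLHIV precision is worse still, ±15.3 at 80% and ±11.4 at 90%.

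The documents do not support saying that ±5% fails at every completion rate, because the expected proportion and confidence level are not given. Nor do they prove that the design effect was omitted. The match of both counts with design effect 1 is strong circumstantial evidence and no more.

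**What to change.** Keep enrolment as it is. In Participants and sampling:

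- Replace the precision sentence with the 95% half-widths that the design delivers per country and stratum, with design effect 2 and the stated loss. Give them at the completion proportion assumed for each stratum and at 50% as the worst case (±9.5 for 268; ±13.0 for 141). State the assumed proportions and the confidence level, and say whether women lost are excluded or counted as untreated.
- Before printing any WLHIV precision, reconcile 141 with 15% of 440: state the WLHIV positivity that was used (141 implies 32%), or use 66 (±19.1 at 50%).
- Delete the 80% power, or name the hypothesis and difference to which it refers.
- Do not rescue ±5% by attaching it to an estimate pooled over countries. The article sizes the study in each country and describes no pooled estimate as the basis of the sample size.

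The cost is wording only. No further women are needed, and the stated precision becomes less favourable.
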